5.2 SCREENING FOR IGT

5.2.1 Population selected for screening. Cases of IGT to be studied will be found by population screening. The type of population screened will vary from one Clinical Center to another; some will select a sample representative of the general population while others will select subjects thought to be at high risk of IGT (eg, subjects who are obese, have hypertension, or have relatives with type 2 diabetes).

5.2.2 Conditions for the screening examination. Prior to the screening examination, any acute intercurrent illness or injury must be resolved and treatment of any chronic condition (such as hypertension, arthritis or hyperlipidemia) must be stabilized so that the test is performed under stable conditions.

5.2.3 The oral glucose tolerance test.

The OGTT should be administered in the morning after at least three days of unrestricted diet and usual physical activity. The test should be preceded by an overnight fast of 10-16 hours, during which water may be drunk. Smoking is not permitted during the test. The presence of factors that influence interpretation of the results of the test must be recorded (e.g., medications, inactivity, infection, etc.). In the first screening OGTT blood glucose may be analysed from capillary whole blood with a Hemocue-analyser, which is fast, easy, cheap, and yet reliable method in blood glucose screening.

After collection of the fasting venous blood sample (or capillary blood sample in the first OGTT), the subject should drink 75 g of anhydrous glucose (or partial hydrolysates of starch of the equivalent carbohydrate content or 82.5 g glucose monohydrate) in 250-300 ml of water over the course of 5 minutes. Venous (or capillary) blood samples will be collected at 1 and 2 hours after the test load (only at 2 hours in the first screening OGTT).

The blood sample should be collected in a tube containing NaF and centrifuged within 15 minutes to separate the plasma; the plasma should be kept at 4oC up to 12 hours or frozen until the glucose concentration is measured. In addition, at fasting a blood sample will be collected in a tube containing EDTA for measurement of HbA1c by high pressure liquid chromatography (HPLC).

Subjects with previously known IGT can be tested by this proce­dure to determine if they still have IGT, but must be excluded if they have been actively treated for IGT (see Section 5.1.2).

The test will be interpreted and acted on as follows:

1. Subjects with 2hr plasma glucose (or capillary whole blood glucose) <7.4 mM (<133 mg/dl) will be told that they have normal glucose tolerance, are ineligible for the study, and that no further action is indicated.

2. Subjects with 2hr plasma (or capillary whole blood) glucose 7.4‑11.3 mM (133-199 mg/dl) are asked to come to another OGTT after at least one week. Subjects with mean 2hr glucose 7.8-11.0 of two OGTTs are

diagnosed as having IGT and are further evaluated for eligibility to partic­ipate in the DPS.

3. Subjects with mean 2hr glucose >11.1 mM (>200 mg/dl) are diagnosed as having probable diabetes and are referred to the usual source of medical care for confirmation and treatment of diabetes.

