3.2 SUBJECT ELIGIBILITY AND EXCLUSION CRITERIA

3.2.1 Definitions of diabetes and IGT. The classification of and diagnostic criteria for diabetes and other categories of glucose tolerance will be based on criteria adopted by the World Health Organization (WHO), (World Health Organization, 1985). According to WHO criteria, the diagnosis of diabetes may be established on the basis of:

1) casual plasma glucose concentrations  11.1 mM (200 mg/dl) on one occasion with symptoms or on two without,

2) fasting venous plasma glucose concentrations  7.8 mM (140 mg/dl) on more than one occasion, or

3) oral glucose tolerance tests meeting the criteria shown in Table 3.1. IGT is diagnosed when the criteria for diabetes are not met, but the 2 hour post‑load plasma glucose is from 7.8 to 11.0 mM (140 to 199 mg/dl).

TABLE 3.1. DIAGNOSTIC VALUES FOR THE ORAL GLUCOSE TOLERANCE TEST

ACCORDING THE WORLD HEALTH ORGANIZATION (WHO)

Venous plasma glucose concentration

mM mg/dl

IGT Fasting < 7.8 <140

and 2 hour 7.8‑11.0 140‑199

Diabetes Fasting > 7.8 >140

or 2 hour >11.1 >200

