6.2 MONITORING FOR COMPLIANCE AND ENDPOINTS

6.2.1 Interim visits. Interim monitoring will be for the primary purposes of improving compliance with the diet-exercise therapy. Interim visits will take place at 1, 2, and 3 months after randomization and thereafter every three months for the duration of the study. When this schedule coin­cides with the annual examinations (i.e. at months 12, 24, 36, 48, 60, and 72), the interim and annual examinations will be combined into a single visit.

At the interim visits, subjects will be seen by a dietitian or nurse for assessment of general health and measurement of body weight. No physical examination or laboratory tests will be performed unless a physician considers this to be indicated. Dietary, exercise, and weight loss counseling will be provided according to the assigned diet-exercise treatment.

The interim visits can be conducted in usual medical clinics, community centers, or patients' homes, as needed to ensure compliance.

6.2.2 Annual examination and OGTT.  The primary end point (diabetes) will be assessed annually as described under the Annual Examination (Section 5.4). The results of the OGTT at the annual exam should be interpreted as follows:

1. If the results are normal or indicate IGT (i.e. fasting plasma glucose <7.8 mM (<140 mg/dl) and 2hr plasma glucose <11.1 mM (<200 mg/dl), then continue the assigned treatments.

2. If the results are diagnostic of diabetes (i.e. fasting plasma glucose >7.8 mM (>140 mg/dl) or 2hr plasma glucose >11.1 mM (>200 mg/dl), then repeat the OGTT after one week. If the repeat test results are normal or indicate IGT, then resume the assigned treatments.  If they are diagnostic of diabetes, the subject has reached the study endpoint.

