7.1 WORSENING FROM IGT TO DIABETES

This will be defined by the results of an oral glucose tolerance test which is diagnostic of diabetes (i.e. fasting plasma glucose > 7.8 mM or 2 hr plasma glucose > 11.1 mM). Confirmation by a repeat OGTT after seven more days is required, as described in Section 6.4.2.

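### Screening rule 1 in Protocol 5.2.3 gives an all-clear on the 2-hour glucose alone, even when a venous fasting value reaches the diabetic limit of Table 3.1 (minor, screenee safety)

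*Protocol*

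**What the plan says.** Protocol 5.2.3 gives three rules for acting on the screening OGTT.

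- **Rule 1:** with a 2-hour value below 7.4 mM (133 mg/dl), people "will be told that they have normal glucose tolerance, are ineligible for the study, and that no further action is indicated".
- **Rule 2:** a 2-hour value of 7.4 to 11.3 mM leads to a second OGTT.
- **Rule 3:** a mean 2-hour value above 11.1 mM is treated as probable diabetes and referred to usual care for confirmation.

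None of the three states a fasting condition. A fasting specimen is nevertheless part of the test: "After collection of the fasting venous blood sample (or capillary blood sample in the first OGTT"). The specimen at the first test may differ from later ones: "In the first screening OGTT blood glucose may be analysed from capillary whole blood with a Hemocue-analyser".

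The diagnostic definition is in 3.2.1 and Table 3.1, headed "Venous plasma glucose concentration". The diabetes row begins "Diabetes Fasting > 7.8 >140" and joins the 2-hour limit by 'or'. The IGT row begins "IGT Fasting < 7.8 <140", so even IGT requires a fasting value below the limit. The glossary in Appendix A defines diabetes by the same table.

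**The concern.** Rule 1 does more than exclude. It tells a person that glucose tolerance is normal and closes the case. If the fasting value from that same test lies in the protocol's own diabetic range, the message contradicts the protocol's definition, and the person loses the repeat test or referral that the result warrants.

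Rule 3 shows that the protocol already accepts responsibility for referring probable diabetes found at screening. Rule 1 withholds that route from people whose abnormality is in the fasting limb. What is at stake is false reassurance of a screenee, not the trial's inference.

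**Working it through.** No sample size, power or event figure is involved. The check applies the written rules to one test result.

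**Inputs**

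- Rule 1 cut-off (5.2.3): 2-hour below 7.4 mM, no fasting condition.
- Diabetic limits (Table 3.1, venous plasma): fasting 7.8 mM or 2-hour 11.1 mM.
- Units: 140 / 7.8 = 17.9 and 133 / 7.4 = 18.0 mg/dl per mM, so the two cut-offs are printed on the same scale.

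**Step 1. Example.** First screening OGTT on venous plasma: fasting 8.2 mM, 2-hour 7.2 mM.

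| Source | Test applied | Result |
|---|---|---|
| 5.2.3 rule 1 | 7.2 < 7.4 | normal, ineligible, no further action |
| 3.2.1 / Table 3.1, diabetes row | 8.2 > 7.8 | diabetic OGTT |
| 3.2.1 / Table 3.1, IGT row | fasting < 7.8 required | not met |

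Table 3.1 prints a strict sign at 7.8. Whether exactly 7.8 counts does not affect the example.

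**Step 2. Could another rule catch this person at the first OGTT?**

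| Rule | Requires | Met by 8.2 / 7.2? |
|---|---|---|
| 5.2.3 rule 2 | 2-hour 7.4–11.3 | no |
| 5.2.3 rule 3 | mean 2-hour > 11.1 | no |
| 5.1.1(a), third OGTT | first 2-hour > 7.8 | no |
| 5.1.1(b) | fasting 6.4–7.7 and 2-hour 7.8–11.0 | no |
| 5.1.1(c) | 2-hour 7.8–11.0 on the OGTT | no |
| 3.4 | discharges ineligible subjects only | no retest or referral |

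The third-OGTT rule is the only one that uses a fasting value to order a retest. It needs a first 2-hour value above 7.8, and rule 1 needs one below 7.4, so the two cannot overlap at the first OGTT. HbA1c is also collected at the OGTT, but no rule acts on it.

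**Step 3. How unusual is the pattern?** It needs fasting of at least 7.8 and 2-hour below 7.4, so fasting minus 2-hour exceeds 7.8 − 7.4 = 0.4 mM. In the example the difference is 8.2 − 7.2 = 1.0 mM. The glucose two hours after a 75 g load must be lower than the fasting value. That should be uncommon, but the documents give neither its frequency nor the number to be screened.

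**Step 4. Illustration from follow-up.** For an enrolled subject at an annual visit, 6.2.2 covers the same result: "If the results are diagnostic of diabetes (i.e. fasting plasma glucose >7.8 mM (>140 mg/dl) or 2hr plasma glucose" above its limit leads to a repeat OGTT after one week. This shows how the protocol handles the finding elsewhere. It is not a second contradiction.

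**The case against.** The strongest case on the other side is that rule 1 is triage in a population screen for IGT, a condition identified by the 2-hour value, and that triage may differ from endpoint ascertainment. In part this stands. A reader might infer that rule 1 also contradicts 6.2.2 and 7.1, since 7.1 too speaks of a test "diagnostic of diabetes (i.e. fasting plasma glucose > 7.8 mM or 2 hr plasma glucose > 11.1 mM". Those sections govern enrolled subjects, so they do not conflict with a screening rule. The conflict is with 3.2.1 and Table 3.1, which define the diagnosis without limiting it to follow-up. The triage argument explains why such a person is not enrolled. It does not justify telling that person that tolerance is normal.

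A second objection is that the first OGTT may be capillary. This stands as a limit. Table 3.1 classifies venous plasma, and the protocol states no capillary threshold for diabetes, so no contradiction is shown on that route. Capillary testing is optional, however, so a venous first test is within the protocol. The documents do not say what share of first tests would be venous.

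A third is that one high fasting value is not established diabetes. That is correct: it is an unconfirmed result that calls for a repeat, and rule 1 removes the occasion for one.

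**Conclusion.** The inconsistency is real, narrow and minor. For a venous first OGTT with 2-hour glucose below 7.4 mM and fasting glucose at the diabetic limit, rule 1 gives an all-clear that the protocol's own definition does not support, and no other screening rule corrects it.

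The conclusion rests on reading rule 1 as written and on a venous specimen. That the pattern is rare is a judgement from the required fall of more than 0.4 mM; no figure in the documents confirms it.

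A reader might infer that people with diabetes enter the trial through this rule, or that the results could be biased. The documents do not support that. Rule 1 makes these people ineligible, so the randomized comparison, the endpoint and power are unaffected. The point concerns rule 1 only and makes no claim about who is enrolled through the other branches.

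**What to change.** Limit rule 1 to people with 2-hour glucose below 7.4 mM **and** fasting venous plasma glucose below the Table 3.1 diabetic limit of 7.8 mM. People at or above that limit remain ineligible, but are either given a repeat venous test or referred to their usual source of care, as rule 3 already provides.

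For a capillary first OGTT, the sponsor should state the fasting value that triggers a venous repeat. That value should not be read off the paired plasma and capillary ranges in 5.1.1(c). Those are eligibility ranges for a sample after at least 4 hours without food, whereas the OGTT follows a 10 to 16 hour fast. The plasma range also stops at 7.7 mM, so 7.8 lies outside it.

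The cost is one added condition, one stated capillary trigger, and a few extra referrals or repeat tests. The fasting sample is already drawn, and nothing changes in randomization or analysis.

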2.1 INTRODUCTION

IGT is a condition defined by an abnormal response to an oral glucose tolerance test. Although persons with IGT do not show any manifes­tations of diabetes and are not considered to have diabetes (which can be diagnosed by a more extreme abnormality of glucose tolerance), IGT is clinically important because persons with IGT are at increased risk of developing diabetes and coronary heart disease. In 1980 the World Health Organization (WHO) adopted a classification of diabetes and other categories of glucose tolerance, which was revised in 1985 (World Health Organization, 1985). The two common types of diabetes are type 1, or insulin‑dependent diabetes, and type 2, or non-insulin‑dependent diabetes.  Diabetes can also be secondary to other diseases.

In addition to a new classification, new diagnostic criteria for diabetes and IGT have been widely adopted.  The diagnosis of diabetes may be established on the basis of casual plasma glucose concentra­tions 11.1 mM (200 mg/dl) or the presence of fasting venous plasma glucose concentrations 7.8 mM (140 mg/dl) on more than one occasion, or by oral glucose tolerance tests meeting the criteria shown in Table 3.1.  IGT is diagnosed when the criteria for diabetes are not met, but the 2 hour post‑load plasma glucose is from 7.8 to 11.0 mM (140 to 199 mg/dl).

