3.5 REGISTRATION, RANDOMIZATION, AND STRATIFICATION

3.5.1 Treatment assignment and registration. Assignment will be issued by the Clinical Center which will register enrollment of subjects upon verification that all eligibility criteria have been met.

3.5.2 Randomization to treatment. Subjects will be randomly allocated to special or standard diet-exercise program in the following way:

Group 1: Special diet - exercise

Group 2: Standard diet - exercise

3.5.3 Stratification. Randomization will be stratified by 1) Clinical Center and 2) the 2-hour post-load glucose obtained during the OGTT:

o Stratum 1: venous plasma glucose = 7.8-9.4 mM (140-169 mg/dl)

o Stratum 2: venous plasma glucose = 9.5-11.0 mM (170-199 mg/dl)

3.5.4 Registration. Subjects are enrolled in the DPS as soon as they are registered by the Clinical Center. The Clinical Center will promptly register a subject upon verification that all eligibility criteria have been met. A registration number (and treatment assignment) is given to the subject according to the randomization list.

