5.1.1 Eligibility criteria

o **Impaired glucose tolerance defined as follows**:

**a**) the mean of 2-hour plasma glucose of two OGTTs >7.8 and <11.0. If the mean is <7.8, and the 2-hour value of the first OGTT is >7.8 and the 2-hour value of the second OGTT is <7.8 and the fasting plasma glucose of the second OGTT is >5.5, then a third OGTT is performed and the mean 2-hour glucose is counted for the first and third OGTT

**OR**

**b**) one OGTT with fasting plasma glucose 6.4-7.7 and 2-hour value 7.8- 11.0

**OR**

**c**) random plasma glucose value after at least 4 hour fast 6.4-7.7 (or capillary blood -> 5.6-6.4) and one OGTT with 2-hour value 7.8-11.0.

o **Obesity, defined by body mass index >25 kg/m2**

o **Age 40-64 years**

o Willingness, after receiving a thorough explanation of

the study, to participate. Subject indicates willingness by signing the consent form.

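### Minor: rule 2 in Protocol 5.2.3 gives the upper limit for recall to a second OGTT as 11.3 mM and as 199 mg/dl, and the two do not convert

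*Protocol*

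**What the plan says.** Section 5.2.3 lists three rules for acting on the screening OGTT.

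- Rule 1: subjects with a 2-hour value "<7.4 mM (<133 mg/dl) will be told that they have normal glucose tolerance" and leave the study.
- Rule 2: subjects with a 2-hour value from 7.4 to "11.3 mM (133-199 mg/dl) are asked to come to another OGTT after at least one week". IGT is then judged on the mean of the two tests, with limits of 7.8-11.0 and no mg/dl figure.
- Rule 3: "Subjects with mean 2hr glucose >11.1 mM (>200 mg/dl) are diagnosed as having probable diabetes" and are referred to their usual care.

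Elsewhere 199 mg/dl always goes with 11.0 mM. Sections 2.1 and 3.2.1 both define IGT by a 2-hour value where "plasma glucose is from 7.8 to 11.0 mM (140 to 199 mg/dl"), and the upper randomization stratum in 3.5.3 is "venous plasma glucose = 9.5-11.0 mM (170-199 mg/dl").

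For entry, 5.1.1(a) requires "the mean of 2-hour plasma glucose of two OGTTs >7.8 and <11.0". Route (b) accepts "one OGTT with fasting plasma glucose 6.4-7.7 and 2-hour value 7.8" to 11.0, and route (c) also needs one OGTT with a 2-hour value of 7.8-11.0. Section 5.1.1 gives no mg/dl figures.

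**The concern.** Rule 2 is an operative threshold, not background text, and it prints two different upper cut-offs for one decision. A centre working in mM and a centre working in mg/dl would treat a first 2-hour value of 11.1-11.3 mM differently: the first would recall the subject and the second would not.

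The recall matters for such a subject. The first test is above the range that routes 5.1.1(b) and (c) require of a single OGTT, so that test can count towards entry only through the mean in 5.1.1(a). That mean needs the second OGTT which rule 2 controls. What is at stake is a few eligible people who might not be retested.

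**Working it through.** **Inputs.** Six other pairs of glucose limits in the protocol: 7.8/140 and 11.0/199 (sections 2.1 and 3.2.1), 11.1/200 (2.1, 3.2.1 and rule 3), 9.4/169 and 9.5/170 (3.5.3), and 7.4/133 (rules 1 and 2). The pair under test is 11.3/199 (rule 2).

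**Step 1: can one conversion factor fit all pairs?** With mM (m) rounded to 0.1 and mg/dl (g) rounded to 1, a printed pair is compatible with factors from (g - 0.5)/(m + 0.05) to (g + 0.5)/(m - 0.05).

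| Pair (mM / mg/dl) | Factor range |
|---|---|
| 7.4 / 133 | 17.79-18.16 |
| 7.8 / 140 | 17.77-18.13 |
| 9.4 / 169 | 17.83-18.13 |
| 9.5 / 170 | 17.75-18.04 |
| 11.0 / 199 | 17.96-18.22 |
| 11.1 / 200 | 17.89-18.15 |
| **11.3 / 199** | **17.49-17.73** |

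The first six share the interval 17.96-18.04. The rule 2 upper pair lies wholly below it, so rounding does not explain the mismatch.

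**Step 2: size of the mismatch.**

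- 11.3 mM is 11.3 × 17.96 = 203.0 to 11.3 × 18.04 = 203.9 mg/dl. With the usual factors it is 11.3 × 18.0 = 203.4 or 11.3 × 18.016 = 203.6.
- 199 mg/dl is 199/18.04 = 11.03 to 199/17.96 = 11.08 mM.
- The gap is therefore about 4 to 5 mg/dl, or 0.22-0.27 mM. In values recorded to 0.1 mM it covers 11.1, 11.2 and 11.3.
- The lower end of the same band is sound: 7.4 × 18.0 = 133.2.

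**Step 3: could a subject in the gap still qualify?** A two-test mean of 7.8-11.0 needs a second value between 15.6 - first and 22.0 - first.

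| First value (mM) | Second value giving a mean of 7.8-11.0 (mM) |
|---|---|
| 11.1 | 4.5-10.9 |
| 11.2 | 4.4-10.8 |
| 11.3 | 4.3-10.7 |

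For example, 11.2 followed by 9.0 gives a mean of 10.1, which is IGT. The lower bounds are not strict, because 5.1.1(a) adds a third-OGTT route for some means below 7.8.

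**Step 4: which figure is out of place?** In mM, the recall band is wider than the IGT range at both ends: 7.4 against 7.8, and 11.3 against 11.0. In mg/dl, the lower end moved with it, from 140 to 133, while the upper end stayed at the IGT figure of 199. A wider band suits a rule that judges eligibility on a mean, since a first value just outside 7.8-11.0 can still average inside it.

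**Step 5: which rule covers the gap if 199 mg/dl is used?** Rule 1 does not apply and rule 2 does not apply. Rule 3 acts on a mean, and only one value exists. The same is true of a first value of 11.4 or 13 mM when 11.3 mM is used.

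**The case against.** The strongest reply is that this is an editorial slip with almost no practical effect. The mM figure leads and the mg/dl figure is in parentheses. The IGT sentence in the same rule and all of 5.1.1 give no mg/dl figure. Harm requires a centre to follow the secondary unit against the primary one. This stands, and it is why the point is minor.

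A reader might go further and infer three things that the protocol does not support.

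- **That the mismatch leaves these subjects without any rule.** The lack of a stated action for a single high first value comes from rule 3's use of a mean, and it exists under either unit. The mismatch only decides whether 11.1-11.3 mM falls on the recalled side. Table 3.1 also classes a 2-hour value above 11.1 mM as diabetic, so a clinician has some guidance. If rule 3 is read loosely to cover a single value, the mg/dl limit sends the subject to referral instead of a retest; the two limits still lead to different actions.
- **That the intended limit is fully open, with 11.0 mM as likely as 11.3 mM.** The protocol does not explain the choice, but the widened lower end and the two-test mean both point to 11.3 mM.
- **That ineligible subjects could enter or the comparison could be affected.** Rule 2 only governs recall. Entry still depends on 5.1.1, and the step comes before randomization.

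**Conclusion.** The point holds as a minor error. The upper limit in rule 2 is wrong as written by about 4 mg/dl, whichever figure is kept, and the protocol's own pairs are enough to show it. The consequence is confined to first 2-hour values of 11.1-11.3 mM, which are recalled under one unit and not under the other although they can still lead to eligibility.

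That 199 mg/dl is the figure left uncorrected is an inference from the shape of the band, not a statement in the protocol. How many screened subjects fall in the gap cannot be derived, because no distribution of 2-hour glucose is given. The treatment comparison, sample size and endpoint are not affected.

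**What to change.** In rule 2 of 5.2.3, keep 11.3 mM and change the parenthesis to 133-203 mg/dl. The choice of 203 keeps whole mg/dl values at or below the mM limit: 203/18.0 = 11.28 mM, while 204/18.0 = 11.33 mM. If 11.3 mM is instead converted with 18.016 and rounded (203.6), 204 is acceptable. A one-line confirmation from the sponsor is sensible.

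Do not lower the limit to 11.0 mM. That would make the units agree, but only by excluding first values of 11.1-11.3 mM from recall in both of them.

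The cost is one corrected figure. The missing action for a single first value above the recall limit is a separate matter of rule 3's wording, which this correction does not settle.
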